## Abstract

**Background:**

This protocol is based on home health care (HHC) best practice evidence showing the value of coupling timely post-acute care visits by registered nurses and early outpatient provider follow-up for sepsis survivors. We found that 30-day rehospitalization rates were 7 percentage points lower (a 41% relative reduction) when sepsis survivors received a HHC nursing visit within 2 days of hospital discharge, at least 1 more nursing visit the first week, and an outpatient provider follow-up visit within 7 days compared to those without timely follow-up. However, nationwide, only 28% of sepsis survivors who transitioned to HHC received this timely visit protocol. The opportunity exists for many more sepsis survivors to benefit from timely home care and outpatient services. This protocol aims to achieve this goal.

**Methods:**

Guided by the Consolidated Framework for Implementation Research, this Type 1 hybrid pragmatic study will test the effectiveness of the Improving Transitions and Outcomes of Sepsis Survivors (I-TRANSFER) intervention compared to usual care on 30-day rehospitalization and emergency department use among sepsis survivors receiving HHC. The study design includes a baseline period with no intervention, a six-month start-up period followed by a one-year intervention period in partnership with five dyads of acute and HHC sites. In addition to the usual care/control periods from the dyad sites, additional survivors from national data will serve as control observations for comparison, weighted to produce covariate balance. The hypotheses will be tested using generalized mixed models with covariates guided by the Andersen Behavioral Model of Health Services. We will produce insights and generalizable knowledge regarding the context, processes, strategies, and determinants of I-TRANSFER implementation.

**Discussion:**

As the largest HHC study of its kind and the first to transform this novel evidence through implementation science, this study has the potential to produce new knowledge about the impact of timely attention in HHC to alleviate symptoms and support sepsis survivor’s recovery at home. If effective, the impact of this intervention could be widespread, improving the quality of life and health outcomes for a growing, vulnerable population of sepsis survivors. A national advisory group will assist with widespread results dissemination.

## Background

Sepsis is a life-threatening acute organ dysfunction secondary to infection [1]. Acute care hospitals in the United States (US) discharge over 1.5 million sepsis survivors annually [1–4]. Across diverse healthcare systems, 30-day hospital readmission rates are consistently high for survivors [5–9]. Sepsis is a serious illness and survivors are vulnerable to substantial post-discharge morbidity and mortality [10], with readmission rates rivaling those for heart failure, pneumonia, and myocardial infarction [5, 11, 12]. Annual health care costs for sepsis survivors are nearly double the costs of these other conditions [12]. Sepsis survivors are twice as likely as non-sepsis patients to be readmitted by 30 days [12], often with a new or recurrent infection [13] with 32% of these 30-day readmissions occurring within 7 days [6, 14], and in-patient costs alone ranging $23.7 [15] to $27 billion per year [16] making sepsis the costliest inpatient diagnosis in the US [17]. When hospitalized, these vulnerable, mainly older adults, are exposed to increased risk for hospital-acquired infections and medical errors [18]. Sepsis survivors often experience impaired functional status [19], reduced quality of life [20], and accelerated cognitive decline [20], all of which are associated with a shortened life span [21]. A subset of sepsis survivors, especially those who experience these complex sequelae, may greatly benefit from goals of care discussions and palliative care [22, 23].

Annually, up to one-third of sepsis survivors transition from acute care to skilled home health care (HHC) where nurses monitor for reinfection, support uninterrupted medication management, manage symptoms, and work with patients, caregivers, and other providers to support continued recovery [6, 24]. Vigilant, timely community-based monitoring to address subtle changes in symptoms, conduct medication reconciliation, and reinforce the plan of care is necessary to prevent avoidable hospital admissions and keep patients at home. While as many as one-third of sepsis survivors are prescribed HHC after hospital discharge [24], there is wide variability in the intensity and timing of HHC visits for this vulnerable population [25]. Medicare Conditions of Participation require that HHC agencies conduct the first home visit within two days of referral or the patient’s return home, or on the physician-ordered start of care date. Therefore, agencies typically have considerable latitude in determining the timing and volume of services provided [25–28]. Agencies may measure timeliness of the first visit by when they “accept” the referral, versus when received or by facility discharge date. In doing so, patients may not be seen for more than two days after discharge, as our prior work indicates.

It is during the first few weeks of HHC that sepsis survivors are most at risk for rehospitalization [14], indicating the need for timely attention to symptom management afforded by HHC services following hospital discharge. Frontloading, defined as early and intensive nursing visits and endorsed by The National Association for Homecare & Hospice [29, 30], Visiting Nurse Associations of America [31], The Home Health Quality and Improvement National Campaign [32], and The Institute for Healthcare Improvement [33], has been recommended as an industry standard for decades. While 64% of HHC agencies claim to be utilizing frontloading [30], our national Medicare claims studies found that only 23% of heart failure [34], 44.7% of sepsis [24] and 39% of patients overall [34] received frontloaded nursing visits when the timing was measured from the hospital discharge date. Our results indicate that while frontloading has been promoted as a best practice for high-risk populations, it is not widely or consistently implemented across HHC agencies nationally.

The first homecare visit, usually conducted by a registered nurse, is one of the most critical steps of the home care episode [35, 36], and is important for continuity of care [18, 37, 38]. Too often the HHC nurse conducts the admission visit with fragmented, incomplete, or inaccurate knowledge of the patient’s clinical condition [39, 40]. In our prior work, among sepsis survivors readmitted by 30-days, 33% of hospital readmissions occurred within 7 days. Moreover, we found a mismatch between the hospital diagnoses and the HHC diagnoses, indicating HHC clinicians may not know the patient is a sepsis survivor [14]. For hundreds of thousands of sepsis survivors, the most frequent diagnoses in HHC were pneumonia and urinary tract infection, with sepsis ICD codes appearing only 4% of the time [14]. Further, most of the 7-day readmission risk factors identified by our team were noted after the HHC admission [14]. It is too late to wait for the HHC assessment to occur on the first home visit (which could occur several days after hospital discharge and be available to others in the record up to 5 days later). Providing high quality information from the acute care referral source to increase awareness of the sepsis survivors facilitates accurate care planning and supports provision of earlier visits, higher quality care, and prevention of avoidable, early rehospitalization for a sizable and increasing population of sepsis survivors [41–44]. The National Consensus Project Clinical Practice Guidelines for Quality Palliative Care support access to palliative care throughout the trajectory of severe illnesses like sepsis, increasingly in community or home settings. Improving the transfer of information can increase access to these resources, which can enable patients and families to receive support in their homes [45]. For these reasons, our intervention starts in acute care to improve identification of the sepsis survivor and to highlight the diagnosis for HHC clinicians.

Physicians must certify the eligibility of patients for HHC, and review and sign the orders for care [46]. Currently, there is no requirement that the physician ordering HHC must see the patient other than the relatively new requirement for a single face-to-face encounter that can be up to 90 days before or 30 days after initiation of HHC services. In general, early outpatient provider visits for patients discharged from acute care vary in timing from 2 days [47] to 30 days [48] and are most effective for those at highest risk [49]. Patients are more likely to attend an outpatient provider visit if scheduled before leaving the hospital [47]. Despite this evidence, our experience is that patients are often expected to schedule outpatient visits themselves. In our studies, for home health patients, outpatient provider follow-up alone, within 7-days, without nursing visits occurred only 24.2% [50] of the time for heart failure patients and 11% of the time for sepsis survivors [24].

Our prior evidence indicates that neither early HHC nursing nor outpatient provider visits alone significantly reduced hospital readmissions in two high-risk populations (heart failure and sepsis). In contrast, when the two practices were combined, early hospital readmissions were significantly reduced. In our prior comparative effectiveness study using national Medicare data and an instrumental variable analysis approach, we found 30-day rehospitalization rates were 7 percentage points lower (41% relative reduction) for sepsis patients when a HHC nursing visit was received within 2 days of hospital discharge, at least 1 more nursing visit the first week, and an outpatient provider follow-up visit by 7 days occurred compared to those without timely follow-up [14, 24].

The literature suggests a critical need to implement best practices to increase awareness of sepsis survivors and to improve the delivery of timely care during transitions [14, 39–43]. However, no previous studies have targeted the sepsis survivor in HHC. Based on the high impact of our prior work, we are investigating the effectiveness and implementation of the Improving Transitions and Outcomes of Sepsis Survivors (I-TRANSFER) intervention to increase the proportion of sepsis survivors receiving this powerful combination of two best practices. To advance the science of transitional care for sepsis survivors, this protocol will test the effectiveness of these practices in the real world and study its implementation with a pragmatic, multi-center, Type 1 hybrid design in partnership with five dyads of acute care and HHC providers. As the largest study of its kind in HHC, it will produce new knowledge about the real-world effectiveness and implementation determinants; and will focus on an understudied process (transition to and care in HHC) and an understudied population (sepsis survivors) to tackle a large, costly, and common rehospitalization challenge where little evidence exists. Many HHC agencies do not have the resources to study how to optimize transition of care processes. Therefore, our study findings will bring process and structure to a very common transition procedure and inform the HHC industry with knowledge that could apply to other disease states. If shown to be effective, information on context, barriers likely to be encountered, other determinants, and the most feasible strategies for implementation will inform the hospital and HHC industries for widespread implementation of an effective practice.

Our I-TRANSFER intervention is designed to address several barriers and gaps that may jeopardize the implementation of early post-acute surveillance. Sepsis survivors are not consistently identified with a medical diagnosis of sepsis until after discharge from acute care [51–55]. This results in the diagnosis and other patient characteristics not being adequately communicated to the next level of care [1, 39, 40, 56]. Home health clinicians likely do not know they are receiving a sepsis survivor. Second, there is little evidence to guide the transition of sepsis survivors to HHC. Our protocol is designed to provide a critically needed, especially post-pandemic, best practice intervention model to clinicians and the HHC industry nationwide. This protocol is even more timely given the pandemic, as research suggests that COVID-19 can lead to sepsis [57] and many hospitalized patients prefer to recover at home due to skilled nursing facility capacity and safety concerns [58]. Third, among sepsis survivors transitioned to HHC, and not readmitted within the first week, only 28% received the early visit protocol, shown by our team to be associated with significantly reduced readmissions [24]. This presents an important opportunity to generate further evidence of effectiveness and inform widespread implementation to help many more sepsis survivors. Our advisory group, comprised of national leaders in sepsis care and HHC professional organizations will facilitate widespread dissemination of our findings, from academic nursing and medicine to industry practitioners.

## Methods

### Study aims and hypothesis

#### Aim 1, effectiveness of the I-TRANSFER intervention

Aim 1 of our study is to test the effectiveness of the I-TRANSFER intervention compared to usual care on 30-day rehospitalization and emergency department (ED) use among sepsis survivors receiving HHC. We hypothesize that compared to usual care, sepsis survivors who receive the I-TRANSFER intervention will have significantly fewer all-cause 30-day rehospitalizations, inpatient days if rehospitalized, and ED visits within 30 days of hospital discharge.

#### Aim 2, I-TRANSFER implementation

Aim 2 of our study is to produce insights and generalizable knowledge regarding the context, processes, strategies, and determinants of I-TRANSFER implementation. We will assess readiness of the sites using the Organizational Readiness for Implementing Change (ORIC) survey. The ORIC survey includes 12 questions related to the participant’s perception of their organization’s readiness to implement the intervention including characteristics like confidence, motivation, support, flexibility, addressing challenges, and coordination [59]. We will study the implementation using qualitative methods guided by the Consolidated Framework for Implementation Research (CFIR) [60]. We will also test two process hypotheses. First, compared to usual care, sepsis survivors receiving I-TRANSFER will have sepsis identified as a HHC diagnosis on the Outcomes Assessment Information Set (OASIS) significantly more often. Second, sepsis survivors receiving I-TRANSFER will receive early and intense HHC nursing visits (within 2 days of hospital discharge + 1 more that week) and community provider visits by 7-days more often. The OASIS is a comprehensive assessment tool, mandated by the Centers for Medicare and Medicaid (CMS), designed to collect nearly 100 items related to a home health recipient’s functional status, clinical status, and service needs at several time points during a HHC episode [34].

### Conceptual framework

#### Aim 1, effectiveness of the I-TRANSFER intervention

As illustrated in Fig. 1, the Andersen Behavioral Model of Health Services [61] will guide Aim 1. Service use is modeled as a function of health care system factors, and individual determinants. Health services system determinants include resource and organizational factors. Community and market characteristics (e.g., the supply of HHC agencies, physicians, and other health services) are some examples of system resources. Organizational factors include HHC agency and hospital characteristics such as whether the agency is owned by a hospital, part of a chain, or it operates as a for-profit, nonprofit or government entity. The Organizational Readiness for Implementing Change (ORIC) survey results will be a factor in this domain. Implementation determinants (barriers, enablers, strategies) from the CFIR domains discovered in Aim 2 may also be added to the model as variables to understand their impact on the outcomes.

**Fig. 1 Fig1:**
[figure not shown]
Andersen Behavioral Model of Health Services. Health services system determinants

There are three types of Individual Determinants in the Andersen framework. Predisposing factors include age, sex as a biological variable, race, and informal support, for example. Enabling factors include facilitators of the use of health care services (e.g., health insurance, income). Need/illness level includes health status such as acute and chronic disease, cognitive and physical functioning, symptoms such as pain and anxiety, and recent prior hospitalizations. Determinants in the Andersen framework will also be considered for risk adjustment and when forming our national, covariate-balanced control sample (Aim 2). Conceptually, the outcomes are jointly determined by the determinants in the Andersen framework as well as the home health and physician services provided during the HHC episode. Because sicker patients are more likely to use more HHC and physician services and are likely to have worse outcomes – that is, the receipt of increasing levels of HHC and physician services is endogenous – a simple comparison of outcomes will yield misleading biased results and are taken into consideration in the analytic plan.

#### Aim 2, I-TRANSFER implementation

The Consolidated Framework for Implementation Research (CFIR) guides Aim 2 and contains 5 constructs to assess context and implementation determinants at each site. Context has been defined as the set of circumstances or unique factors that surround a particular implementation effort [60] and anything external to the intervention which impedes or strengthens its effects [5, 62]. Determinants are factors that might prevent or enable practice change including barriers, enablers, incentives or disincentives [60, 63]. Processes and strategies are the workflows and interventions applied to address determinants and achieve the implementation [63].

### Study design

The study was designed based on evidence from our previous study; extensive preliminary work with national data, hospital, and HHC stakeholders; & implementation science literature [24, 25, 34, 50, 60, 64–72]. The study is a pragmatic, Type 1 hybrid design, that primarily evaluates effectiveness via Aim 1, with an observational, implementation component integrated into its design via Aim 2. This novel research design is being increasingly used in the evaluation of service delivery type interventions, especially when conditions are heterogeneous and traditional randomization of individuals is not possible [73]. This pragmatic design involves an initial period in which no sites are exposed to the intervention followed by a six-month onboarding period, a 12-month intervention period, and a 6-month maintenance period. In the initial proposal we planned a stepped wedge cluster randomized trial but due to the COVID-19 pandemic the 2020 cohort are unsuitable as a comparison cohort requiring extension of the inclusion dates for the comparison dataset to 2021–2024, and staggered rollout required by stepped wedge design is no longer feasible to finish the study on time.

Sepsis survivors transitioned to the participating HHC agencies during the period before implementation serve as the usual care control group compared to those exposed to I-TRANSFER, the intervention group. To address historical threats and to increase generalizability, we form control comparison groups from national Medicare clinical and administrative claims data within and outside our partner sites to compare to our intervention group: 1) one year prior to any contact with our team; 2) during the onboarding period, and 3) across the entire study period. Observations on survivors from outside our partners’ sites will be weighted using entropy balancing [74–76] to produce a covariate-balanced comparison group.

Each hospital and HHC agency dyad will assemble a site implementation team comprised of key stakeholders and project champions involved in the planning and implementation. The principal investigator and at least two other research team members will visit each site in person and stay in close phone or email contact with the site coordinator and team for onboarding and Aim 2 data collection. Additional contacts may occur if needed. We have planned 12 in-person visits and frequent, standardized phone, virtual and/or email contacts. Expected site stakeholders may include, for example, a programmer to write a query to identify the inpatient sepsis survivors; hospitalists, emergency room physicians, sepsis experts, and ambulatory providers to determine follow-up appointment workflow, and hospital case managers are expected to be important informants overall. On the HHC side, the teams will include a hospital based HHC liaison who facilitates the referrals and transfer of patient information to the HHC agency; an HHC intake nurse who schedules the first visit and assigns the visiting nurses; a HHC nurse who knows the workflow for planning visits and working with patients; an intake director who understands the entire workflow; the Directors of Nursing or Chief Operating Officers who oversee operations. These stakeholders will participate in individual, or group interviews and survey completion as described below. An estimated 60 stakeholders will provide informed consent prior to data collection. A study site coordinator identified by each dyad will assist with communication, scheduling, oversight, and data collection at each site. A project manager will track progress and support the work across all sites. Stakeholder consent to participate will be obtained prior to each interview by the study team member conducting the interview.

Implementation of the I-TRANSFER components will be guided by the stakeholders and research team using intervention mapping, as described below. The context and determinants (barriers, enablers), processes, and strategies encountered during Aim 1 will be collected for Aim 2 analysis. Hospital partners will work with the study and HHC team to achieve the following components of I-TRANSFER: identify the sepsis survivors during the hospitalization, make the outpatient follow-up appointment before discharge, notify the HHC agency of a sepsis survivor, conduct timely home health visits and outpatient visits in week one. Based on our preliminary work, we have identified several effective strategies that we can suggest to better identify the sepsis survivor, including generalizable use of sepsis order sets within the electronic health record [14]. We will also recommend use of the Centers for Disease Control (CDC) Epicenters Sepsis Clinical Surveillance Definition, which has the advantage of identifying confirmed cases of sepsis given the criteria of sustained antibiotic delivery [35, 77, 78]. We will examine fidelity to these recommended components as potential implementation enablers.

Challenges we expect to face in making and achieving a timely outpatient visit are limited appointment availability, and patients who cancel or do not attend the visit. A potential strategy is to increase awareness about I-TRANSFER’s evidence and include a script for the clinician to educate the patient about the value and importance of the outpatient visit. Transportation may be an issue as well and will be brainstormed for solutions with the stakeholders and tracked as a barrier. Hospital based personnel will notify the HHC intake department when the patient is a sepsis survivor. The intervention mapping will determine the workflow for this component with each site. It may include phone calls, text messaging, faxed or electronic documents.

HHC intake personnel will likely schedule the nurse visits and notify the visiting nurse of the sepsis diagnosis and date of the outpatient appointment. To meet protocol, the first registered nurse home visit will occur within 2 days of hospital discharge, with a second visit that week. The patient will be encouraged and assisted if necessary (e.g. transportation) to attend their scheduled outpatient appointment.

A four-member interdisciplinary, national advisory board with expertise in sepsis and HHC will advise the team via teleconference once in year one and twice in years 2–5. They will review the CFIR interview guide, and findings from the onboarding and implementation phases, providing advice as the study progresses. The national advisory board brings expertise in sepsis and HHC and will have a major role in facilitating dissemination of the study findings through access to national stakeholder groups.

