### Study period

Onboarding is a 6-month period when the implementation and research teams plan the implementation. Intervention is the 12-month period when I-TRANSFER is in operation. Maintenance is a 6-month period when the research team assesses whether the intervention continues without research team monitoring and feedback. The analysis will be an intent to treat. We will adjust for time, or any health system interventions, as well as patient covariates that may confound the findings using generalized mixed models.

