In addition to the survivors from the treated dyads in the baseline period, additional control survivors will be used to provide a much larger sample of control observations. These observations will be drawn from the population of Medicare sepsis survivors not being cared for by any of the participating institutions. This sample is unlikely to be balanced on covariates, a priori, with the sample of survivors from participating providers. Therefore, entropy balancing will be used to create sampling weights for these observations to produce balance on covariates. All hierarchical regression analyses will take these entropy balance weights into account. In addition to an intent-to-treat indicator, the regression will include covariates specified by the Andersen Behavioral Model. Inpatient days after the index discharge will be modeled using hierarchical Poisson regression. ED utilization will be modeled using hierarchical logistic regression.

The pragmatic aspects of the study design make it important to conduct various sensitivity and exploratory analyses. Sensitivity analyses will include checks of robustness of findings with and without sepsis survivors who are readmitted shortly after discharge (e.g., within 7 days), those with a resumption of HHC episode, discharges with very short (1 day) or very long hospital stays (30 days or more), and survivors less than 65 years old. Exploratory analyses will include estimation stratified by type of sepsis, sex (as a biological variable), and hospital ownership status.

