## Discussion

Sepsis takes more lives than opioid overdoses, breast cancer, and prostate cancer combined [4]. Prior studies by our team indicate the impact of early HHC nursing combined with early outpatient provider visits but the ability of hospitals and HHC agencies to implement these effective interventions is limited and varied. Our innovative study will be the first to transform the practice paradigm in HHC through implementation of a best practice early visit intervention for growing numbers of sepsis survivors. This study will bring process and structure to a very common transition process – currently many HHC agencies do not have the resources to study how to optimize transition of care processes, our findings will inform the industry and can apply to other disease states. The study focuses on an understudied process (transition to and care in HHC) and an understudied population (sepsis survivors) to tackle a large, costly, and common readmission challenge where little evidence exists.

Our study, however, is not without limitations. It is possible that dyads may begin to implement parts of the protocol prior to the implementation period. However, we believe the specifications of the I-TRANSFER components will be difficult to achieve in full and effectively without collaborative efforts. To be safe, additional specification checks will include treatment indicators in the retrospective control data and onboarding period to determine whether such activities were taking place. We will also ask the status and quality of such interventions prior to onboarding and would recruit a new dyad if it is an issue.

Also, the sample of sepsis survivors from non-participating dyads is a useful comparison group only if the distributions of characteristics of those survivors and their care providers overlap/match with those of survivors from the participating dyads. By using the entire Medicare population, the risk of lack of overlap is minimized. Nevertheless, should lack of overlap be an issue, we will use matching techniques to mitigate this threat. Lastly, we considered a cost analysis but due to budgetary constraints could not include a robust analysis. Instead, we will document whether there are added costs to the dyads such as adding a position, and we will have the data from the claims to roughly compare differences in service utilization such as numbers of HHC visits, outpatient care, or observation stays.

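### The protocol does not settle whether dyad onboarding months belong to the usual-care control, and it leaves their separation to a secondary check

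*Protocol article*

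**What the plan says.** All references are to the protocol article.

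Study design sets out the periods: "This pragmatic design involves an initial period in which no sites are exposed to the intervention followed by a six-month onboarding period", then 12 months of intervention and 6 of maintenance. The same section defines the within-dyad comparator: "Sepsis survivors transitioned to the participating HHC agencies during the period before implementation serve as the usual care control group". It then lists control comparison groups, drawn from inside and outside the partner sites, at three times: "1) one year prior to any contact with our team; 2) during the onboarding period, and 3) across the entire study period". None of the three is named as primary.

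The Aim 1 analysis uses another term for the dyad comparator: "In addition to the survivors from the treated dyads in the baseline period, additional control survivors will be used". The Abstract likewise places a baseline period without intervention ahead of a six-month start-up period. On the model, the Aim 1 analysis says: "In addition to an intent-to-treat indicator, the regression will include covariates specified by the Andersen Behavioral Model". It describes no separate onboarding term.

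Study period describes onboarding as preparation: "Onboarding is a 6-month period when the implementation and research teams plan the implementation". The Discussion concedes: "It is possible that dyads may begin to implement parts of the protocol prior to the implementation period". It offers three answers. The components would be hard to achieve fully without collaboration; "additional specification checks will include treatment indicators in the retrospective control data and onboarding period"; and sites will be asked about such activity before onboarding, with a new dyad recruited if needed.

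**The concern.** The Aim 2 analysis dates implementation from go-live, and the text on implementation mapping speaks of a 12-month implementation phase. Onboarding comes before go-live. The Study design definition of the control therefore takes onboarding in, while the baseline-period wording leaves it out. The primary outcome has two candidate comparators.

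The choice matters because onboarding is not neutral time. Study design describes in-person visits and close contact with the sites, and it expects stakeholders such as a programmer for the sepsis query and clinicians who settle the appointment workflow. In the mapping text, the steps that choose strategies and write implementation protocols come before the monitoring step in the 12-month phase. If parts of the protocol start in these months and the months count as usual care, the comparator's readmission rate falls and the intervention effect is understated.

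**Working it through.** **1. The passages side by side**

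- Includes onboarding: the Study design control definition (everything before implementation), and its second control window, which covers partner sites as well as outside sites.
- Excludes onboarding: the Abstract (baseline, then start-up), the Aim 1 analysis (baseline period), and the first control window in Study design (the year before contact).
- Safeguards: the onboarding indicator is a check on whether early activity took place, and no consequence for the primary estimate is stated. The replacement-dyad step, as worded, deals with activity before onboarding, so it cannot catch adoption during onboarding. The argument that full delivery needs collaboration is weak for a period that is itself collaborative.
- Contrast with maintenance: the Aim 2 analysis gives intervention and maintenance separate treatment indicators. The device is already in use at the other end of the timeline.

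**2. The plan's own figures**

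The Aim 1 sample section gives a 23% control rate and a 7-point reduction, so 23% against 16%, and 7/23 = 30.4%, as stated. It asks for 400 patients per time interval without giving alpha, sidedness or power. The pooled two-proportion formula is

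n = [z(α)·√(2·0.195·0.805) + z(β)·√(0.23·0.77 + 0.16·0.84)]² / 0.07².

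It gives 396 for one-sided 5% and 80% power, and 502 for two-sided 5% and 80%, both without clustering. The 400 is thus matched only by the assumed one-sided variant. The dilution below does not depend on it.

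**3. Dilution of the within-dyad contrast**

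Let w be the onboarding share of dyad control records and f the share of the full effect already present in onboarding. Then

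observed contrast = 7 × (1 − w·f) points.

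The baseline length for the pooled control and f are not in the document. Assumed: 12 baseline months, 6 onboarding months and an even monthly flow, so w = 6/18 = 1/3. The case w = 1 treats partner-site onboarding as the only comparator.

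| f | w = 1/3 | w = 1 |
|---|---|---|
| 0 | 7.0 | 7.0 |
| 0.10 | 6.77 | 6.30 |
| 0.25 | 6.42 | 5.25 |
| 0.50 | 5.83 | 3.50 |
| 1 | 4.67 | 0 |

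**4. What exclusion costs**

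With 12 intervention months, the standard error without onboarding relative to that with it is √(1 + 1) / √(1 + 1/1.5) = 1.095, about 10% wider.

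Two-sided 5% power, taking the stated 869 per period as 869 per 12 months (an assumption, since the period length is not given) and ignoring clustering:

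| Control | f = 0 | 0.10 | 0.25 | 0.50 | 1 |
|---|---|---|---|---|---|
| 18 months, onboarding kept | 98.1% | 97.5% | 96.1% | 92.5% | 78.4% |
| 12 months, onboarding out | 95.8% | 95.8% | 95.8% | 95.8% | 95.8% |

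Up to about f = 0.25, keeping onboarding costs no power. Above that it does. The bias is present for every f above zero.

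**The case against.** A reader might infer that the primary analysis definitely counts onboarding as usual care, so that the primary contrast is already diluted. The document does not support that. The sentence defining the control does not name onboarding, the Aim 1 analysis says baseline period, and onboarding is listed separately from the pre-contact year and is not said to be pooled with it. This stands, and it is why the point is an unsettled definition rather than a known bias.

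The size is also conditional. The Discussion concedes only that parts may start early, and the Background reports that neither early nursing visits nor outpatient visits alone significantly reduced readmissions. Partial adoption could therefore leave f near zero. No adoption fraction can be taken from the document, so the values above are illustrations and zero belongs among them.

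A loss of power is a further tempting claim. It fails at modest adoption: at f = 0.25 power is about 96% whether onboarding is kept or dropped. Survivors from non-participating sites are untouched by early adoption in the dyads and would reduce the dilution in the full model, by an amount that cannot be computed from the article.

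Finally, an onboarding indicator, once fitted, does remove those months from the reference level, and an unseen analysis plan might place it in the main model. But this article assigns it to additional checks and describes the main model with an intent-to-treat indicator and covariates. The conflict between the two control definitions remains.

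**Conclusion.** The concern holds as an inconsistency in the definition of the dyad control, joined to a safeguard that sits outside the primary model. If onboarding months are pooled as control, the within-dyad contrast shrinks by about 0.2 to 1.2 points out of 7 for f between 0.10 and 0.50, and not at all for f = 0. This rests on the assumed 12 plus 6 months and an even flow of discharges, and it leaves out the outside controls. Any bias from early adoption runs toward no effect. The larger losses in the w = 1 column would apply only to a comparison that used partner-site onboarding alone, which the protocol lists but does not make primary. The change is worth making because it removes a foreseeable bias cheaply. The case does not rest on power.

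**What to change.** In the primary model, define dyad usual care as discharges in the year before any contact with the study team, a window that Study design already lists, and use the same term in the Abstract, Study design and the Aim 1 analysis. Give dyad onboarding months their own indicator, as the Aim 2 analysis does for maintenance, or exclude them. Make the model that counts onboarding as control the sensitivity check. Drop only the partner-site onboarding comparison, and keep outside-site survivors from that calendar window as concurrent controls.

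The cost is one indicator and a few words of text. Under the assumed period lengths, one-third of the pooled dyad control records leave the reference group, which widens the within-dyad standard error by about 10% before national controls are added.
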